## Abstract

**Background:**

Currently, oral targeted therapies are known to be effective and are frequently used to treat metastatic cancer patients, but fatigue is a frequently reported early side effect of these treatments. This fatigue may impact the patient’s treatment adherence and result in a negative impact on quality of life. Physical exercise significantly improved the general well-being and quality of life of advanced cancer patients. However, there is no specific physical activity program adapted for patients with advanced disease.

**Methods:**

QUALIOR is a two-part, randomized, open-label, and multicenter with two arms phase II/III trial. Patients (phase II: *n* = 120; phase III: *n* = 312) with metastatic cancer (breast cancer, kidney cancer, lung cancer, and other cancers [including but not limited to colon cancer, melanoma, sarcoma, or hepatocarcinoma]) treated with a first- or second-line oral targeted therapy without chemotherapy will be included. Patients will be randomized (2:1) to a 3-month supervised home-based standardized physical activity program or to a recommended adapted physical activity (via a booklet). The primary objective of the phase II is to evaluate the feasibility of the supervised program. The primary objective of the phase III is the evaluation of the benefit of the supervised home-based program compare to the recommended program in terms of fatigue and quality of life at 3 months. The secondary objectives aim to evaluate the impact of the supervised program on fatigue over time, pain, physical capacities, psychosocial and cognitive functions, general quality of life, frequency of dose reduction and patients’ adherence to the targeted therapy, overall survival, and progression-free survival. This study will also evaluate the medico-economic impact of supervised program compared to the recommended adapted physical activity program.

**Discussion:**

The aim of this study is to evaluate home-based physical exercise program for metastatic cancer patients treated with oral targeted therapies to help patients to cope with fatigue and improve quality of life.

**Trial registration:**

This trial was registered in ClinicalTrials.gov since May 2017 (NCT03169075).

## Background

Oral targeted therapies (OTT) are effective and frequently used to treat metastatic cancer patients, including metastatic kidney, lung, breast, colon cancer, and melanoma as well as sarcomas [1]. These new-targeted therapies have specific tolerance profiles that differ from those of chemotherapies. Fatigue is one of the major early side effects of OTT. For example, fatigue was reported in 90% of renal cancer patients treated with antiangiogenic tyrosine-kinase inhibitors [2], 60% of breast cancer patients treated with everolimus [3], and in most of the patients that received vemurafenib to treat melanomas [4]. Fatigue results in a decreased quality of life (QoL) and may influence treatment adherence, thus it is important to proposed patients with strategies to prevent and reduce fatigue.

Supervised physical exercise programs (SPEP) followed by patients with localized breast, colon, and prostate cancer have shown an association between an increased overall survival, and significant reduction of fatigue and increased QoL. Several studies revealed that physical exercise significantly improved the general well-being and QoL of advanced cancer patients treated with chemotherapy or hormonal therapy [5]. Only one pilot study was conducted among advanced metastatic cancer patients treated with targeted therapy. This pilot study involving metastatic non-small cell lung cancer patients suggested that physical exercise was feasible and had a positive impact on QoL [6]. For the majority of these studies, the physical activity last for a 3-month period but without standardization of the program [7]. Recent guidelines recommend evaluation and optimization of standardized exercise programs although most of them have been developed for patients with non-metastatic cancer during or after treatments. The majority of these programs were designed for groups or for home-based individual session (with different supports such as video, booklet, or website), but without personalized follow-up. However, for metastatic cancer patients, a category of frail patients, physical activity in groups is not always feasible and the implication of a coach is a major factor for patients’ acceptation of and compliance to a home-based program.

Fatigue reported by patients treated with OTT may be linked with their body mass index (in relation with decrease protein synthesis leading to loss of muscle mass) [8]. Several studies demonstrated a relation between body mass index and survival outcomes in patients treated with targeted therapies for metastatic cancers [9–11]. Furthermore, physical activity may improve patients’ muscle mass, muscular strength, and physical and social components of QoL [12].

The QUALIOR trial is a two parts study which aim to evaluate the feasibility of home-based SPEP assisted with a coach on a 3-month period for patients with metastatic cancer receiving a first- or a second-line OTT (phase II) and the efficacy of this home-based SPEP on patient’s fatigue and QoL (phase III) compared to the recommended program.

## Aim and research questions

The phase II is a randomized non-comparative study to evaluate the feasibility of a home-based, adapted, standardized, and supervised physical exercise program for patients receiving OTT for a metastatic solid tumor (spared in 4 cohorts: breast cancer, kidney cancer, lung cancer, and other cancers [including but not limited to colon cancer, melanoma, sarcoma, or hepatocarcinoma]). The comparative phase III study aims to evaluate the benefit of a SPEP compared to a recommended adapted physical activity, on fatigue and physical dimension of quality of life of such patients at 3 months.

In both phase II and III, the secondary objectives will include the evaluation of the impact of the SPEP on overall and progression-free survival, general quality of life over time, fatigue over time, pain, psychosocial and cognitive functions, muscle mass, muscle density, adipose tissue (visceral and subcutaneous), weight gain, and body mass index. The physical benefit, patients’ observance and tolerance, and the predictive value of the SPEP on survival, general quality of life, and fatigue will also be evaluated. Investigations will also address the toxicity, frequency of dose reduction, and patients’ adherence to the targeted therapy. Finally, this study aims to explore the correlation between fatigue and muscle mass, and between fatigue and muscle density.

The QUALIOR study also encompasses an ancillary evaluation of the medico-economic impact of the SPEP.

## Methods/design

### Study design

QUALIOR is an open phase II-III, non-blinded, randomized, and multicenter with two arms study (Fig. 1).

**Fig. 1 Fig1:**
[figure not shown]
Study design. A baseline assessment will be performed between the initiation of the OTT and the randomization by the clinician (C0) and the educator (E0). Other assessment will be performed monthly by the clinician (C1, C2, C3) and the educator (E1, E2, E3) at the end of month 1 (M1), M2, and M3, respectively. The different assessments will be performed at the hospital

### Participant eligibility

#### Inclusion criteria

Eligible patients must be 18 years or older, treated for a metastatic solid tumor, should have received a maximum of two lines of chemotherapy for their metastatic solid tumor, and could have been prescribed a first-line oral targeted therapy. The choice of the oral targeted therapy (that can be associated with hormonal therapy), within the list of drugs with market authorization, is at the investigator discretion. Targeted therapies can include oral anti-angiogenic agents, epithelial growth factor inhibitors, and cyclin-dependent kinase inhibitors. Patients should have a hemoglobin level ≥ 9 g/dL, Eastern Cooperative Oncology Group (ECOG) performance status ≤2, controlled pain, and life expectancy ≥3 months. Patients must be able to comply with the constraints of the standardized supervised physical activity protocol at home and signed informed consent form before study entry. Oral hormonal therapy is not considered as a targeted therapy.

#### Exclusion criteria

comprise patients with known risk of fracture, symptomatic cardiac insufficiency (NYHA-3), respiratory insufficiency (grade 3), intense pain not controlled with analgesic treatment, neuropathy (grade 3), history of cancer in the past 5 years (except basal cell carcinoma adequately treated and in situ cervical cancer treated and cured), or bone metastases with risk of fractures. Patients previously treated with longer than 1 month corticosteroids (dose > 1 mg/kg) before randomization, as well as patient receiving oral targeted therapy with concomitant chemotherapy, or injectable targeted therapy cannot be enrolled in this study. Geographical, sociological, or psychological reasons that could potentially hamper adherence with the study protocol and follow-up schedule, history of non-adherence to medical treatment, reluctance or incapability to conform to the study protocol, and deprivation of liberty or guardianship are also criteria of exclusion.

#### Oral targeted therapies

Investigators will decide which oral targeted therapy best fit their patients’ metastatic disease. The prescribed oral targeted therapies, that must have received marketed authorization, include, but are not limited to the following inhibitors: antiangiogenic tyrosine kinase, epidermal growth factor receptor (EGFR), cyclin-dependent kinases, BRAF, ALK, mTOR, and PARP.

### Interventions

#### Experimental arm (SPEP): program A

All participants in the experimental arm will have to start the SPEP session within 15 days following the initiation of the oral targeted therapy.

This program will last 3 months with a total of 12 SPEP sessions (one weekly) plus 24 non-supervised exercise sessions (twice a week). An expert coordinator coach has elaborated three levels of difficulties for this program.

The home-based SPEP sessions are composed of two dimensions: development of the musculoskeletal strength and patients’ endurance (muscular reinforcement of the cardiorespiratory system). These sessions will be supervised by a coach (trained physical educator or physiotherapist) specifically trained for this study, with respect to the pathology and the clinical study. Before each SPEP session, using a visual analogic scale, the coach will determine the patient’s level of fatigue to adjust the intensity, the repetition, and the speed of execution of the exercises proposed during the 60-min session. The coach will report the information of duration and intensity of the sessions in a standardized document.

Between each SPEP session, patients will follow two non-supervised exercise sessions (planned with the coach) consisting of a minimum of 30 min and maximum of 60 min of walk, running, or biking, depending on the patient’s level of fatigue (estimated by patients themselves). For these non-supervised sessions, the coach will provide patient with a heart rate monitor (connected watch) and a dedicated booklet containing personalized physical activity recommendations.

#### Control arm (recommended adapted physical activity): program B

Patients randomized in the control arm will receive a booklet containing general physical activity recommendations to reduce the fatigue resulting from cancer treatments (including some proposition of exercises): information and advice to adapt daily routine, preserve valuable time with family and friends, and maintain physical activity to ensure well-being without exceeding their limits. Patients could choose the exercises to follow within the booklet. Each session proposed in the booklet will last 30 min minimum.

### Study outcomes

#### Primary outcome

##### ***Feasibility****,* phase II non-comparative study

The feasibility will be assessed using the rate of patients that participated adequately in the SPEP. The SPEP participation will be considered sufficient if the patient complete at least 50% of the theoretically planned sessions in the 3 months (supervised and non-supervised).

##### ***Efficacy****,* phase III comparative study

The co-primary endpoint is the fatigue score (using FACT-F questionnaire) and the physical well-being score (using FACT-G questionnaire) evaluated after 3 months. A difference of at least 2.5 points for FACT-F and at least 5 points for the physical well-being score of FACT-G will be considered clinically significant. SPEP superiority over the recommended adapted physical activity program will be demonstrated if at least one of the targeted dimensions (FACT-F or the physical well-being of the FACT-G) is significantly improved without deterioration of the other dimension.

#### Secondary outcomes

Progression free survival is defined as the time from randomization to date of disease progression or death of any cause, whichever occurs first.

Overall survival is defined as the time from the date of randomization to date death of any cause.

Toxicity of the targeted therapy will be assessed using the NCI-CTCAE v4.03. Data concerning the class, frequency, and severity of adverse events will be collected and analyzed. The data will be collected at baseline, monthly during the 3-month program, then every 3 months during the first year of follow-up.

Adherence to targeted therapy will be evaluated by the Morisky-Green questionnaire at baseline then monthly during the 3-month program. This questionnaire, composed of six items related to patient’s adherence to the scheduled treatment, is regularly used to evaluate adherence to oral therapies. Scoring is performed through sum of item scores. Higher scores indicate better adherence to treatment.

For the outcomes described below, patients will fill the French versions of the specific questionnaires at baseline, monthly during the 3-month program, then every 3 months during the first year of follow-up, otherwise indicated. For each questionnaire but EQ-5D-3L, scoring is performed through a simple sum of item scores using the scoring recommendations of the authors.

Quality of life (QoL) will be assessed using the FACT-G and the 3-level version of EuroQol-5D (EQ-5D-3L) questionnaires. FACT-G is composed of 27 items related to patient’s general well-being grouped into four well-being subscales: physical, social/family, emotional, and functional. One score is generated for each subscale and a global QoL score is generated from all items corresponding to the total FACT-G score. For each dimension, a higher score represents a better QoL level. EQ-5D-3L consists of a patient self-rate health on a visual analogue scale (VAS) plus a descriptive system of five dimensions: mobility, self-care, usual activities, pain/discomfort, and anxiety/depression. Each dimension has three levels of perceived problems. Patient decision results into a 1-digit number for each dimension that can be combined into a 5-digit number that describes the patient’s health state.

Fatigue will be assessed using the functional assessment of cancer therapy-fatigue (FACT-F; 13 items related to patient’s fatigue) questionnaire and the VAS (fatigue; 0–10 scale). For the FACT-F questionnaire, a higher score represent a lower level of fatigue while for the VAS, a higher score represent a higher level of fatigue. For the experimental arm, in addition to the above mentioned schedule, the coach will systematically evaluate the patient’s fatigue by VAS before and after each home-based supervised session.

Pain will be evaluated by VAS (pain; 0–10 scale), a higher score represent a higher level of pain. For the experimental arm, in addition to the above mentioned schedule, the coach will systematically evaluate the patient’s pain by VAS before and after each home-based supervised session.

The physical benefit will be assessed using a rating grid and the short version of the international physical activity questionnaire (IPAQ). The rating grid take into account the physical activity progression plus the physical performance: the 6-min walking test, muscle strength using a dynamometer, muscle function (resistance, flexibility, and stability), and biometry (body mass index, muscle mass index, and amount of body fat). To evaluate patients, the coach will use this grid at baseline then monthly during the 3-month program. The short version of the IPAQ, which comprises four generic items to collect data on patient’s health–related physical activity, will be completed at baseline, month 3 of the program (M3), then every 3 months during the first year of follow-up.

Psychological and cognitive functions will be evaluated using the hospital anxiety and depression scale (HADS) and the functional assessment of cancer therapy–cognitive function (FACT-Cog) version 3 questionnaires. The HADS is a 14 items questionnaire: 7 items related to anxiety and 7 items related to depression scored on a scale. Scores for each subscale (anxiety and depression) range from 0 to 21 and the entire scale (emotional distress) range from 0 to 42, with higher scores indicating more distress. The FACT-Cog is a self-assessment questionnaire to estimate memory, attention, concentration, language, and thinking abilities. This questionnaire, composed of 37 items consists of four subscales: cognitive impairments perceived by the patient (20 items), comments from others (4 items), cognitive abilities perceived by the patient (9 items), and impact on quality of life (4 items). Higher scores indicate greater impairment of cognitive functions.

Body composition will be evaluated by the body mass index and imaging technique described by Martin et al. [13]. Imaging data of visceral adipose tissue, sub-cutaneous adipose tissue, skeletal muscle mass, and skeletal muscle density obtained by computed tomography of thorax, abdomen and pelvis (CT-TAP) scan at baseline, 3 months, and 6 months will be centrally reviewed. Since normal values for skeletal muscle mass, adipose tissues, and threshold values determining sarcopenia are gender-dependent, results from men and women will be analyzed separately.

Anorexia and food intake will be evaluated using the anorexia/cachexia subscale (A/CS) of the functional assessment of anorexia/cachexia therapy (FAACT) questionnaire. The 12 items of the FAACT-A/CS are scored on a 5-point Likert scale. A lower score indicates less appetite. The VAS for appetite will also be performed at baseline and at M3. A state of anorexia will be validated if the FAACT-A/CS score is ≤37 or if the VAS ≤7 [14].

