### Study visits

Patients will be monitored from the date of their randomization until the date of death, withdrawal of consent, or loss to follow-up. The investigators will perform checkup (C) while the coaches will perform evaluation (E). Before any physical exercise, the coach has to monitor patient’s resting pulse rate, oxygen saturation, and blood pressure. Table 1 details the examinations and visits schedule.

**Table 1 Tab1:** Examinations and visits schedule

	Baseline	Physical activity program period			Follow-up 1 (1st year)	Follow-up 2 (5 last years)^a^
		M1	M2	M3		
Inform Consent form	●					

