#### Inclusion (baseline) visit

Eligible patients with signed informed consent form will have baseline visit at the hospital. Baseline checkup and evaluation will be performed the same day before patient randomization.

Checkup (C0):
Clinical examinationsParaclinical examinationsBiological testsQuestionnaires: VAS (fatigue, pain, and food intake), FACT-G, FACT-F, FACT-Cog, EQ-5D-3L, FAACT-AC/S, and HADSBlood samples for translational research (if consented)

Evaluation (E0):
Physical capacitiesQuestionnaires: VAS (fatigue and pain) and IPAQ

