#### Interventional visits

During the intervention phase, the investigator and coach will perform the following checkups and evaluations:
➢ C1 and E1: 1 month ±3 days from SPEP initiation [experimental arm] or randomization [control arm]➢ C2 and E2: 2 months ±3 days from SPEP initiation [experimental arm] or randomization [control arm]

Monthly checkup and evaluation will be performed during the same day for each visit.

Monthly checkup (C1, C2): At the hospital, for all patients.
Clinical examinationsBiological testsQuestionnaires: VAS (fatigue and pain), FACT-G, FACT-F, FACT-Cog, EQ-5D-3L, FAACT-AC/S, and HADS

Weekly evaluations: At home, for patients in the experimental arm only.
Resting pulse rateQuestionnaires: VAS (fatigue and pain)

Monthly evaluations (E1, E2): At the hospital, for all patients.
Physical capacitiesQuestionnaires: VAS (fatigue and pain)

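### Coaches both deliver the SPEP and run the effort-dependent physical tests in both arms, so the secondary physical-benefit comparison is at risk of bias towards SPEP

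*Protocol article*

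**What the plan says.** All references are to the protocol article.

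- **Blinding (Study design):** "QUALIOR is an open phase II-III, non-blinded, randomized, and multicenter with two arms study".
- **Who delivers the SPEP (Experimental arm, program A):** there are 12 weekly supervised sessions at home. "These sessions will be supervised by a coach (trained physical educator or physiotherapist) specifically trained for this study". The coach also adjusts how hard each session is to the patient's fatigue.
- **Who measures (Secondary outcomes, physical benefit):** the rating grid combines physical activity progression, the 6-minute walk, dynamometer strength, muscle function and biometry. "To evaluate patients, the coach will use this grid at baseline then monthly during the 3-month program".
- **Division of work (Study visits):** checkups (C) go to the investigators and evaluations (E) to the coaches. The Fig. 1 legend gives E1, E2 and E3 to the educator.
- **Which patients (Interventional visits):** "Monthly evaluations (E1, E2): At the hospital, for all patients". E3 repeats the physical-capacity tests at month 3 (End of study visit).
- **Baseline (Inclusion visit):** "Baseline checkup and evaluation will be performed the same day before patient randomization".
- **Control arm (program B):** patients receive a booklet, and no coached sessions are described.

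**The concern.** The walk, strength and function tests depend on how hard the patient tries, and effort responds to the person giving the test. By month 3 an SPEP patient has had up to 12 sessions with a coach. A control patient has met a coach only at the evaluations. The tester belongs to the role that delivers the intervention, is not blinded, and may be the patient's own trainer. Encouragement and familiarity can then differ between arms, most plausibly in favour of SPEP.

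Physical benefit is a named secondary objective, and a positive result would be cited in support of the programme. A difference caused by testing conditions would look like a gain in capacity. No later analysis could separate the two, because the distortion is already in the recorded value.

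**Working it through.** **Reading the sections together**

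1. The trial is non-blinded, so a tester at E1 to E3 can know the arm.
2. The coach role delivers the SPEP, and the same role performs E0 to E3 in both arms.
3. The article states no rule that separates a patient's trainer from that patient's tester.
4. E0 comes before randomization, so knowledge of the arm cannot affect it. A distortion at E1 to E3 therefore passes in full into the change from baseline, and baseline adjustment does not remove it.
5. FACT-F and FACT-G are completed by patients and are listed under the investigators' checkups. The tester therefore does not touch the co-primary scores.
6. Exposure differs within the outcome. The walk, strength and function tests are the most exposed and biometry less so. The IPAQ is a patient questionnaire.

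**Illustration of sensitivity**

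The article gives no figure for this bias. The only documented inputs are the phase III size, the 2:1 ratio and the 5% loss to follow-up.

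*Check of the plan's size.* The standardized difference is 2.5/6.5 = 5/13 = 0.385. With two-sided alpha 2.5%, power 80% and 2:1 allocation:

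controls = (2.241 + 0.842)² × 1.5 / 0.385², which rounds up to 97.

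That gives 97 + 194 = 291 patients, and 291/0.95 rounds up to 307. The stated 312 (four cohorts of 78) is within 2% of this, so it is a usable input.

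*Precision.* 312 × 0.95 ≈ 296 evaluable, or about 98.7 control and 197.3 SPEP.

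SE = √(1/98.7 + 1/197.3) = 0.123 SD.

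*Chance of a significant result favouring SPEP when there is no true effect.* This is 1 − Φ(1.96 − b/SE), where b is the assumed shift. The two-sided 5% level is also an assumption, since the article states no level for the grid.

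| Assumed shift b (SD) | b/SE | Chance of a result favouring SPEP |
|---|---|---|
| 0 | 0 | 2.5% |
| 0.1 | 0.81 | 12.5% |
| 0.2 | 1.62 | 36.8% |
| 0.3 | 2.43 | 68.2% |

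The table shows how sensitive a trial of this size is to a modest systematic shift. It is not evidence that such a shift exists.

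**The case against.** The strongest reply is that this is an ordinary limitation of an open-label trial, described in a condensed article. Several parts of that reply stand.

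- **Same person.** A reader might infer that each SPEP patient is tested by his or her own trainer. The article names a role, not individuals. Training takes place at home and testing at the hospital, so different people are compatible with the text. What stands is that no stated rule ensures it.
- **Bias as a fact.** A reader might conclude that the comparison is biased by a known amount. The text supports a risk and a likely direction only. The percentages above are the power of a z-test against shifts that were assumed.
- **Coach-judged progression.** It is tempting to say that coaches grade the activity-progression item themselves. The article does not say how that item is derived, so the point does not rest on it.
- **Test script.** Standard instructions may be in the full protocol or an operating manual. Their absence from the article is not held against the plan.
- **Consequence.** No success criterion depends on the grid. Phase II is judged on session completion and phase III on patient-completed scores.

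The reply does not dispose of the overlap itself. Giving delivery and measurement to one role in a non-blinded trial is written into the text, and a statistical analysis plan cannot undo it.

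**Conclusion.** The point holds as a risk of bias in one secondary outcome. In E1 to E3 the role that delivers the SPEP also administers effort-dependent tests in both arms without blinding, and no stated rule keeps trainer and tester apart. The likely direction favours SPEP; the size is unknown. Baseline and the co-primary comparison are unaffected by the tester.

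This rests on two assumptions: that effort in these tests responds to the tester, and that no separating rule exists in the full protocol. It is a case for a cheap improvement and does not call the trial's main conclusion into question.

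**What to change.** Add to the description of the evaluations:

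1. Where a centre has two or more trained coaches, E1, E2 and E3 are performed by a coach who does not supervise that patient's SPEP sessions.
2. Test instructions and encouragement are identical in both arms. If the full protocol already says so, cite it.
3. The tester's identity is recorded at each evaluation.
4. The grid comparison is reported as made by assessors who knew the arm.

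Two tempting alternatives should be avoided. The centrally reviewed CT muscle measures should not replace the functional tests, because they measure body composition and are already separate outcomes. A sensitivity analysis by whether tester and trainer are the same person should not be relied on. Control patients have no trainer, so it can split only the SPEP arm, and by a factor that was not randomized.

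**Cost:** no extra staff, one field on the evaluation form, and a scheduling constraint that weighs most on centres with few coaches. Recruitment was under way at publication and phase II patients enter the phase III analysis, so testing conditions would change part-way through; the analysis should note this. The change reduces the risk without removing it, because testers would still know the arm and single-coach centres would be unchanged.
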